|                                          | maintain sustained attention, disorganization of thought, or fluctuating changes in level of consciousness).                   |                       | 4. Fluctuating changes in level of consciousness (+/-) |
| Days of delirium                         | Days with the presence of delirium                                                                                             | Discrete Quantitative | Days                                                   |
| Sedation days                            | Days with sedation                                                                                                             | Discrete Quantitative | Days                                                   |
| Sedation-free days                       | 28 days fewer days of sedation                                                                                                 | Discrete Quantitative | Days
It will be defined as 0 if the patient dies.   |
| Barthel index at hospital discharge      | The Barthel Index is a scale used to measure a person's degree of functional independence in activities of daily living (ADL). | Discrete Quantitative | It will be 0 if the patient dies.                      |
| Days of hospital stay                    | Days of hospital stay                                                                                                          | Discrete Quantitative | Days                                                   |
| Days of ICU stay                         | Days of ICU stay                                                                                                               | Discrete Quantitative | Days                                                   |
| Mortality                                | Death                                                                                                                          | Qualitative Nominal   | Yes or no                                              |
| Time from intubation to start of therapy | Time from intubation to start of therapy                                                                                       | Discrete Quantitative | Days                                                   |

Association between early multimodal therapy and days of mechanical ventilation in the intensive care unit of the Fundación Santa Fe de Bogotá: A randomized controlled clinical trial.

Version 6.0

Fundación Santa Fe de Bogotá

April 8, 2024

|                                                         |                                                                                   |                     |                                                                                                                                                                                                                                                                                                                                                                                                                                                                                 |
|---------------------------------------------------------|-----------------------------------------------------------------------------------|---------------------|---------------------------------------------------------------------------------------------------------------------------------------------------------------------------------------------------------------------------------------------------------------------------------------------------------------------------------------------------------------------------------------------------------------------------------------------------------------------------------|
| Muscle strength with the medical research scale council | Evaluation of muscle strength in critically ill patients                          | Qualitative Ordinal | 
5, normal: full movement against full resistance
 
4+, good (+): full movement against gravity and strong resistance
 
4, good (-): full movement against gravity and minimal resistance
 
3+, regular (+): full movement against gravity only
 
3, regular (-): partial movement only against gravity
 
2, sparse: movement eliminated gravity
 
1 minimal: visible muscle contraction without movement
 
0 absent: total paralysis.
 |
| Dysphagia 72 hours after extubation                     | Dysphagia 72 hours after extubation                                               | Qualitative Nominal | Yes or no                                                                                                                                                                                                                                                                                                                                                                                                                                                                       |
| Oral start time.                                        | Time in which the oral route is started after extubation.                         | Qualitative Nominal | 
1: 12-24 hours
 
2: > 24 hours
                                                                                                                                                                                                                                                                                                                                                                                                                                   |
| Healthcare-associated pneumonia                         | The patient developed healthcare-associated pneumonia during his stay in the ICU. | Nominal qualitative | 
0 = No
 
1 = Yes
                                                                                                                                                                                                                                                                                                                                                                                                                                                    |

|                                                   |                                                                                                                                                                                                                                                                                                                                           |                     |                                                                                                                                                                                                                                                                                                                                                         |
|---------------------------------------------------|-------------------------------------------------------------------------------------------------------------------------------------------------------------------------------------------------------------------------------------------------------------------------------------------------------------------------------------------|---------------------|---------------------------------------------------------------------------------------------------------------------------------------------------------------------------------------------------------------------------------------------------------------------------------------------------------------------------------------------------------|
| Maximum mobility scale at 24 hours.               | Maximum mobility measured by the Johns Hopkins scale (JH-HLM)                                                                                                                                                                                                                                                                             | Qualitative Ordinal | 
8: Walk more than 250 feet.
 
7: You walk more than 25 feet
 
6: walk more than 10 steps.
 
5: Stands for more than a minute.
 
4: can be moved to the chair.
 
3: may be sitting on the edge of the bed.
 
2: can turn over in bed.
 
1: He can only be lying down.
 
It will be 0 if the patient dies.
 |
| Manual dexterity and psychomotor processing speed | The evaluated person makes 20 180° turns to the new model Colombian coin of 200 pesos; (similar to that of 25 US cents) as quickly as possible, using first, second, and third fingers only, the person is expected to perform a minimum of 15 seconds in the dominant hand and 19 seconds in the non-dominant hand
Coin rotation test | Qualitative Nominal | 
0: Integrate
 
1: Altered
                                                                                                                                                                                                                                                                                                                   |
| Assessment of Sensory Integrity                   | Screening of sensitivity (superficial and deep) is                                                                                                                                                                                                                                                                                        | Qualitative Nominal | 
0: Integrate
 
1: Altered
                                                                                                                                                                                                                                                                                                                   |

|                                                |                                                                                                                                                                                                                                                                                                                                                                                                                                                                                                                             |                        |                                    |
|------------------------------------------------|-----------------------------------------------------------------------------------------------------------------------------------------------------------------------------------------------------------------------------------------------------------------------------------------------------------------------------------------------------------------------------------------------------------------------------------------------------------------------------------------------------------------------------|------------------------|------------------------------------|
|                                                | 
carried out through the assessment of cutaneous or tactile sensation, proprioception, and stereognosis (shape, size, and texture) in terms of identification, discrimination, and location of the stimulus.
 
Sensitivity screening suggested by the literature
                                                                                                                                                                                                                                                 |                        |                                    |
| Qualitative assessment of cognitive processing | 
Through standardized evaluation, in a directed activity that evaluates domains of isospacial/executive vision, naming, attention, language, memory, abstraction, and orientation.
 
The version that corresponds to the patient will be used like this:
 
Standard: for people with high school education levels and above.
 
 
• Basic: for people with illiteracy or low education
 
 
Blind: for people with significant impairment of visual function
 | Qualitative
Nominal | 
0: Normal
 
1: Altered
 |

|                                                 |                                                                                                                                                                                                                                                                                                                                                                                                                                                                                                                                                                                                    |                       |                                                                                                                                                                              |
|-------------------------------------------------|----------------------------------------------------------------------------------------------------------------------------------------------------------------------------------------------------------------------------------------------------------------------------------------------------------------------------------------------------------------------------------------------------------------------------------------------------------------------------------------------------------------------------------------------------------------------------------------------------|-----------------------|------------------------------------------------------------------------------------------------------------------------------------------------------------------------------|
|                                                 | processing assessment (Montreal Cognitive Assessment)                                                                                                                                                                                                                                                                                                                                                                                                                                                                                                                                              |                       |                                                                                                                                                                              |
| Quantitative assessment of cognitive processing | 
Through standardized evaluation, in a directed activity that evaluates domains of isospacial/executive vision, naming, attention, language, memory, abstraction, and orientation.
 
The version that corresponds to the patient will be used like this:
 
Standard: for people with high school education levels and above.
 
 
• Basic: for people with illiteracy or low education
 
 
Blind: for people with significant impairment of visual function
 
Cognitive Processing Assessment (Montreal Cognitive Assessment)
 | Discrete Quantitative | Numeric                                                                                                                                                                      |
| Evaluation of functionality in daily activities | The patient's level of autonomy and independence will be assessed in basic daily activities of daily living, determining the level of functionality in these, supported by direct observation, clinical                                                                                                                                                                                                                                                                                                                                                                                            | Qualitative Ordinal   | 
7: Complete independence
 
6: Modified Independence
 
5: Supervised
 
4: Minimum attendance
 
3: Moderate assistance
 
2: Maximum assistance
 |

|                                         |                                                                                                                                                       |                         |                                                    |
|-----------------------------------------|-------------------------------------------------------------------------------------------------------------------------------------------------------|-------------------------|----------------------------------------------------|
|                                         | history, and reference from nursing staff and family/caregiver.

Functional Independence Measure (FIM).                                         |                         | 1: Full attendance                                 |
| Grip strength at the time of extubation | Grip strength of the dominant hand within 24 hours after extubation                                                                                   | Continuous Quantitative | Kilograms

It will be 0 if the patient dies. |
| Failed extubation                       | Inability to breathe spontaneously in the first 48 hours after removal of the artificial airway and the patient is unable to maintain a patent airway | Qualitative Nominal     | Yes or no                                          |
| NIV POS extubation                      | Post-extubation non-invasive ventilatory support within 48 hours                                                                                      | Qualitative Nominal     | NOT = 0

IF = 1                              |
| Prolonged mechanical ventilation        | Invasive mechanical ventilation longer than 14 days                                                                                                   | Qualitative Nominal     | Yes or no                                          |
| Tracheostomy                            | Need to use a tracheostomy tube.                                                                                                                      | Qualitative Nominal     | Yes or no                                          |
| Adult respiratory distress syndrome     | Bilateral alveolar infiltrates with a PAFI less than 300.                                                                                             | Qualitative Nominal     | Yes or no                                          |

|                              |                                                                                                                   |                     |                                                                                                                                                                                                                                                    |
|------------------------------|-------------------------------------------------------------------------------------------------------------------|---------------------|----------------------------------------------------------------------------------------------------------------------------------------------------------------------------------------------------------------------------------------------------|
| Dysphonia at 72 hours.       | Presence of dysphonia 72 hours after extubation.                                                                  | Qualitative Nominal | 0: No
1: Yes                                                                                                                                                                                                                                    |
| OMAHA+                | The use of the OMAHA+ Scale during the process of withdrawing ventilatory support to make the extubation decision | Qualitative Nominal | NOT = 0
Yes = 1                                                                                                                                                                                                                                 |
| Alteration in blood pressure | The patient experiences significant changes in blood pressure during the therapies                                | Nominal qualitative | 0 = No

1 = Hypotension without the requirement for medical management

2 = Hypotension requiring medical management

3 = Hypertension without requiring medical management

4 = Hypertension requiring medical management |
| Cardiac arrhythmias          | The patient had a cardiac arrhythmia during therapy.                                                              | Nominal qualitative | 0 = No

1 = Cardiac arrhythmia without a requirement for medical management

2 = Cardiac arrhythmia requiring medical management                                                                                                       |
| oxygen desaturation          | The patient became desaturated during therapy                                                                     | Nominal qualitative | 0 = No

1 = Oxygen desaturation without requirement for medical management                                                                                                                                                                   |

|                         |                                                                                 |                     |                                                                                                                                                    |
|-------------------------|---------------------------------------------------------------------------------|---------------------|----------------------------------------------------------------------------------------------------------------------------------------------------|
|                         |                                                                                 |                     | 2 = Oxygen desaturation requiring medical management                                                                                               |
| Pain or agitation       | The patient experienced pain or agitation during therapy.                       | Nominal qualitative | 0 = No
1 = Pain or agitation without requiring medical management
2 = Pain or agitation requiring medical management                         |
| Invasive line removal   | The patient accidentally or unscheduled removed an invasive line during therapy | Nominal qualitative | 0 = No
1 = Yes                                                                                                                                  |
| tachypnea               | The patient presented tachypnea during therapy.                                 | Nominal qualitative | 0 = No
1=Tachypnea without the requirement for medical management
2=Tachypnea requiring medical management                                   |
| Neurological impairment | The patient presented with neurological deterioration during therapy.           | Nominal qualitative | 0 = No
1=Neurological deterioration without the requirement for medical management
2=Neurological deterioration requiring medical management |
| Unscheduled extubation  | The patient was extubated unscheduled during the ICU stay.                      | Nominal qualitative | 0 = No
1 = Yes                                                                                                                                  |

|                   |                                                           |                     |                   |
|-------------------|-----------------------------------------------------------|---------------------|-------------------|
|                   |                                                           |                     |                   |
| Bronchoaspiration | The patient aspirated bronchodilators during the ICU stay | Nominal qualitative | 0 = No
1 = Yes |

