The mechanisms of postoperative dysphagia can be multifactorial, involving decreased respiratory capacity due to reduced respiratory and bulbar reserve, deconditioning, and disuse atrophy; the presence of cognitive disorders associated with the use of sedation and medications acting on the central nervous system, either by directly compromising the state of consciousness or by intervening in feedback systems of nerve conduction, ultimately affecting the ability to execute and coordinate precise movements for safe and efficient swallowing; mechanical trauma caused by some invasive measures such as the orotracheal tube or feeding tubes, either at the time of insertion or removal, which increases with prolonged use, inappropriate size selection (oversizing), and frequent traumatic maneuvers in acute contexts. (1,9) Overinflation of the endotracheal tube cuff can compress the arytenoid cartilages or the recurrent laryngeal nerve and dislocate the cricothyroid and/or cricoarytenoid joint, affecting the closure of the laryngeal vestibule. (1,14) Another cause of

Association between early multimodal therapy and days of mechanical ventilation in the intensive care unit of the Fundación Santa Fe de Bogotá: A randomized controlled clinical trial.

Version 6.0

Fundación Santa Fe de Bogotá

April 8, 2024

mechanical trauma that is particularly important in cardiovascular surgery patients is the frequent use of transesophageal echocardiography. (1)

The duration of intubation influences the period of disuse of the bulbar musculature for both speech and swallowing, producing in some cases diffuse atrophy, weakness, and impaired ability to generate the necessary lingual and pharyngeal pressure for bolus propulsion and clearance, putting patients at risk of aspiration. (1,8,10–12) Additionally, endotracheal tubes impede normal swallowing function and active laryngeal elevation, reducing the passive opening of the upper esophageal sphincter, which impedes rapid esophageal passage, contributing to the generation and perpetuation of dysphagia. (10)

In addition to pharyngeal structures, the somatosensory and motor functions of the tongue, which are essential for taste, chewing, swallowing, and speech, can be compromised during ICU stay. (15) This can contribute to dysarthria, dysphonia, dysphagia, chewing disorders, and consequences such as aspiration, pneumonia, dehydration, malnutrition, social withdrawal, and reduced quality of life for these patients. (10,12,15,16)

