## 6.6. Outcomes

### *Effectiveness*

Main outcome: time (days) from intubation to extubating.

- Secondary outcomes:

- Days free of mechanical ventilation until day 28
- Days of delirium until day 28
- Time in ICU with delirium until day 28
- Days of hospitalization with delirium until day 28
- Days of sedation until day 28
- Sedation-free days until day 28
- Extubating failure
- Need for non-invasive mechanical ventilation
- Exploratory outcomes:
- Barthel index at discharge
- Days of hospital stay
- Length of stay in ICU
- Mortality from any cause up to 90 days
- Time from intubation to start of therapy
- Muscular strength measured with the Medical Research Council (MRC) scale
- Dysphagia 72 hours after extubation
- Dysphonia 72 hours after extubation
- Time until initiation of oral administration post-extubation
- Development of healthcare-associated pneumonia,
- Maximum mobility measured by JH-HLM
- Grip strength
- Cognitive function measured using the Montreal Cognitive Assessment (MOCA)
- Evaluation of functionality in daily activities until day 28
- Quick sensitivity and dexterity test

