| Days from the start of ventilatory support to the start of weaning | Days from the start of ventilatory support (intubation) to the start of weaning                                                                                                                   | Discrete Quantitative   | Days                                                                                                                                                                                                     |
| Days of mechanical ventilation                                     | Days of invasive mechanical ventilation                                                                                                                                                           | Discrete Quantitative   | Days                                                                                                                                                                                                     |
| Days free of mechanical ventilation                                | 28 days minus ventilation days                                                                                                                                                                    | Discrete Quantitative   | Days

It will be defined as 0 if the patient dies or has been ventilated for more than 28 days.                                                                                                    |
| Delirium                                                           | For a patient to be considered to have delirium according to the CAM-ICU, both the first criterion (acute alteration in mental status) and at least one of the other three criteria (inability to | Qualitative Nominal     | 
 
1. Acute alteration of mental status (+/-).
 
2. Inability to maintain sustained attention (+/-).
 
3. Disorganization of thought (+/-).
 
 |

|                                          |                                                                                                                                |                       |                                                        |
|------------------------------------------|--------------------------------------------------------------------------------------------------------------------------------|-----------------------|--------------------------------------------------------|

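### The printed delirium rule does not require inattention and has no not-assessable state, so sedated days can be counted as delirium days in three secondary outcomes

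*Protocol*

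**What the plan says.** The variable table in Protocol section 6.11 introduces the rule with "For a patient to be considered to have delirium according to the CAM-ICU" and then asks for "both the first criterion (acute alteration in mental status) and at least one of the other three criteria". The other three are an inability to "maintain sustained attention, disorganization of thought, or fluctuating changes in level of consciousness". The fourth item is coded as "4. Fluctuating changes in level of consciousness", present or absent. The duration variable is simply "Days with the presence of delirium".

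Section 6.6 builds three of its eight secondary outcomes on this variable: "Days of delirium until day 28", ICU time with delirium to day 28, and hospital days with delirium to day 28. Two others in the same list are sedation days and sedation-free days.

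Section 6.7 and Annex 5 record delirium by start and end dates. Annex 5 has no field for the four features, none for RASS and none for a day on which the test could not be done. Section 6.5 (occupational therapy) has a separate tier for patients at RASS -3 or lower, so deeply sedated participants are expected.

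**The concern.** The rule lets a patient be positive on acute mental change and fluctuating consciousness alone, without any sign of inattention or disorganised thought. Sedation that is being adjusted can produce that pair. Nothing tells the assessor what to do with a patient who cannot attempt the attention test. Such a patient may be marked as failing it, which with acute mental change is again a positive day.

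The trial's hypothesis is shorter ventilation. If early therapy shortens ventilation, and sedation with it, fewer sedated days could appear as fewer delirium days with no change in delirium itself. Section 4 cites less delirium as a reported benefit of early mobilization, so such a result would readily be read as a cognitive gain. Under section 6.1 only the day-90 evaluators and the data analysts are blinded, so staff who know the allocation apply this rule at the bedside. Section 6.13 also names delirium as a clinically important candidate for the multivariable Cox model, where the same error would follow it.

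**Working it through.** The protocol attaches no rate, power or sample size to delirium, so there is no stated figure to reproduce. The check has three parts.

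**1. Which patterns are positive.** Number the features 1 (acute mental change), 2 (inattention), 3 (disorganised thought) and 4 (fluctuating consciousness). Four yes/no features give 2^4 = 16 patterns. The printed rule needs feature 1 plus any non-empty subset of the other three: 2^3 - 1 = 7 positive patterns. Three of the seven lack inattention: 1+3, 1+4 and 1+3+4. For comparison only, a rule of 1 and 2 and (3 or 4) gives 3 positive patterns: 1+2+3, 1+2+4 and 1+2+3+4. These are counts of patterns, not of patients.

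**2. How a sedated day can become a delirium day.**
- Sedation level varying: features 1 and 4 present, the others absent. This is positive as printed and negative if inattention is required.
- Patient too sedated to attend: features 1 and 2 marked present, with or without 4. The form offers no alternative code. If 4 is also marked, the pattern 1+2+4 is positive under the printed rule and under the comparison rule alike.

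Requiring inattention therefore closes only the first route. The second closes only with a not-assessable code.

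**3. Illustration of size.** From section 6.3, ventilation lasts 6.1 and 3.4 days, a difference of 6.1 - 3.4 = 2.7 days. The following inputs are assumptions, not in the documents, and are taken as equal in both arms:
- f, sedated share of ventilated days: 0.5 to 0.8
- q, share of sedated days scored positive: 0.1 to 1.0
- D, mean delirium days outside sedation: 1 to 3

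Induced difference in counted delirium days = q × f × 2.7:
- lowest: 0.1 × 0.5 × 2.7 = 0.135, about 0.14 days
- highest: 1.0 × 0.8 × 2.7 = 2.16 days

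Share of counted delirium days that are sedated days, at 6.1 days of ventilation = (q × f × 6.1) / (q × f × 6.1 + D):
- lowest: 0.305 / 3.305 = 9%
- middle (q = 0.5, f = 0.5, D = 1): 1.525 / 2.525 = 60%
- same with D = 3: 1.525 / 4.525 = 34%
- highest: 4.88 / 5.88 = 83%

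A simulation of 200,000 patients per setting used the same ranges, with the SD of ventilation days set at 1.4 (section 6.3) or 5 (assumed). The correlation of counted delirium days with sedation days ran from 0.05 to 0.97, and with ventilation days from 0.02 to 0.91. The overlap could be trivial or dominant, and the documents do not say which.

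**The case against.** Several points on the other side stand.

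- **Fluctuating is not the same as altered.** A patient held steadily at RASS -3 has altered consciousness but need not meet feature 4. A reader might infer that every sedated patient scores as delirious. The text supports only that such a patient can.
- **No size can be claimed.** A reader might also infer that the three outcomes largely re-measure sedation or ventilation time. The documents give no delirium or sedation rates, and the illustration spans 9% to 83%. Delirium after sedation or extubation counts too, since the outcomes run to day 28 and include hospital days.
- **The pattern count does not prove misclassification.** Calling four of the seven positive patterns wrong would require the published CAM-ICU algorithm, which is not in the documents. The comparison rule only shows what changes if inattention is required.
- **Section 4 says little here.** Its remark on "cognitive disorders associated with the use of sedation and medications acting on the central nervous system" concerns the causes of dysphagia and not the scoring of delirium.
- **Sedation is recorded separately.** Start and end dates for sedation and delirium would let an analyst see how far the two overlap. They would not show which of the overlapping days could be assessed.
- **A statistical analysis plan may exist.** It could add a rule for unassessable days. But the case definition is already fixed in the protocol, and a later plan cannot recover a daily state that the form does not collect.

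What remains is that both routes to a sedation-driven positive day are open in the rule and form as printed.

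**Conclusion.** The concern holds in limited form. Followed exactly, the rule in section 6.11 can count sedated days as delirium days. Three of the eight secondary outcomes in section 6.6 can therefore be confounded with sedation and ventilation time, and a between-arm difference in them could not be read as a difference in delirium. If ventilation differed by the planned 2.7 days and delirium outside sedation did not change, the spurious difference would be 0.14 to 2.16 days under the assumed ranges. Which end applies cannot be determined from the documents.

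The primary comparison, a Cox model with group as the only term plus a log-rank test, does not use delirium and is unaffected. The later multivariable model would be affected if delirium is retained. The definition should be corrected, but the trial's main conclusion does not depend on it.

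**What to change.** - In section 6.11, check the rule against the CAM-ICU algorithm that the protocol names. Correct it so that altered or fluctuating consciousness without inattention does not by itself make a positive day.
- Add a third daily state, not assessable, for days when that day's RASS shows the patient is too sedated to attempt the attention test. Count such days as neither delirium nor delirium-free, and report them by arm beside the three outcomes. This is the essential part, because the corrected rule alone would still admit a deeply sedated patient marked 1+2+4.
- Add a daily RASS and a not-assessable field to Annex 5, completed in both arms from enrolment. RASS is now a step that guides therapy, and therapy in the late arm starts at 72 hours under section 6.1, so relying on therapy sessions would leave early days in that arm without a score.

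The cost is one rewritten rule and a small daily addition to the form, with the staff time to complete it. Counted delirium days will fall and some days will carry no delirium status. The RASS field would also serve the exploration by RASS already planned in section 6.13.
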